### Study design

The study is a pair-matched CRCT with four arms. In the five Rwandan districts selected for this study, we assessed 55 health centers to inform study design and site selection. First, we limited the data set to only those with an average of at least 48 first ANC per month, operating on the assumption that this would allow for formation of at least 2-4 ANC groups in the event the health center was allocated to the intervention. This gave us 50 potential health centers. We then limited to those that had more than one ANC provider during ANC days, which reduced the available health centers to 37. In total, 36 health centers (one was not matched to ensure pairing) were selected to participate in the study (see
*Extended data*: File 15)
^18^.

Next data on all other criteria for each health center was used to perform nonbipartite pair matching in R producing a list of strongest potential matches across all criteria. The study team then reviewed the possible matches and agreed on optimal pairings among facilities that had at least 2 ANC providers prioritizing matches with similar volume of ANC1 visits, and similar distance to the nearest district hospital. Within each pair, one facility was randomized to group ANC and PNC using a computer-generated random assignment and the other was randomized to continue delivering the standard models of focused ANC and PNC. Selected health centers were pair-matched based on 1) number of ANC providers, 2) ANC volume 3) delivery volume, 4) proportion of ANC1 before 16 weeks gestation, 5) baseline PTB rate, and 6) availability of key screening tests. Pairs were then further matched into quadruples by the study team based on ANC volume, where one pair within each quadruple was randomly assigned using a computer-generated random assignment to additionally implement basic obstetric ultrasound at the health center and early pregnancy testing at the community level and the other was not. No allocation concealment was used.

Therefore, each study facility has one of the four assignments as illustrated in

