### Sample size

Based on a review of RCT results included in the 2015 Cochrane Review of group versus conventional antenatal care for women
^24^, we assume the intraclass correlation coefficient (ICC) between Arms 1 and 2 and Arms 3 and 4 will be no larger than 0.01. We assume the standard deviation of GA at delivery is no larger than 4.3 weeks under both intervention and control arms. At 5% significance, with 36 facilities, this trial is powered (80%) to detect a 0.5-week difference in GA at delivery with 214 observations (ANC and outcome) per facility. Assuming a follow-up rate of 70%, 306 women per facility will be required. Just over 11,000 women will be recruited and we expect to follow almost 8,000 mother-newborn dyads through the period of the six-week PNC visit. At an average rate of 23 eligible recruits per month per facility, the total study duration will be (a) 14 recruitment months (from the end of May 2017 to August 2018, (b) an additional six to seven months to observe the outcomes of the last cohort of women recruited (February 2019), and (c) three additional months to complete data processing and analysis (May 2019).

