### Statistical analyses

To compare the study groups, socio-demographic and reproductive health characteristics, and health care facility descriptive bivariate analyses stratified by study arm will be conducted using Chi-square and Student’s t-test statistics for categorical and continuous data, respectively. Similar unadjusted bivariate analyses will be presented for the primary and secondary outcomes. Unadjusted, intention-to-treat generalized estimating equations (GEE) linear regression with robust variance estimation analyses will be conducted to assess the effectiveness of the treatment regimen on the primary outcome variable, gestation at delivery, and analogous linear and logistic analyses of will be conducted to assess continuous and categorical secondary outcomes (Model 1). For these outcomes, similar analyses will be conducted to control for design effect (Model 2) and the effects of any additional unforeseen differences in measured study group characteristics (Model 3). Model 3 will include all covariates that are statistically significant and judged as important differences between the study group (e.g. not simply significantly different due to large sample size) as identified by a backward stepwise Wald analysis (Model 3), which removes the covariate least associated with the outcome, and continues in that manner to remove covariates not significantly associated with the outcome at the α=0.05 level.

Model 1: Outcome=Independent Causal VariableModel 2: Outcome=Independent Causal Variable, adjusted for design effectModel 3: Outcome=Independent Causal Variable, adjusted for design effect plus (retained) covariates

Additionally, we propose comparing these methods with data-adaptive targeted maximum likelihood estimators (TMLE)
^25^. These would attempt to leverage the hierarchical structure of the data and would adjust for covariates through a data-adaptive algorithm. Multi-level analyses to adjust for facility-level characteristics will be considered.

The main analyses will compare the control group (Arms 1+2) with the intervention group (Arms 3+4). Subanalyses by study arm will be conducted.

Arm 1: Standard ANC/PNC careArm 2: Standard ANC/PNC care, with early pregnancy testing and ultrasoundArm 3: Group ANC/PNC onlyArm 4: Group ANC/PNC care, with early pregnancy testing and ultrasound

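### Model 3 has two covariate rules that do not fit together: it is meant to adjust for differences between arms, but keeps or drops covariates by their association with the outcome

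*Protocol article*

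**What the plan says.** The Statistical analyses section sets out three models for the primary outcome and each secondary outcome. Model 1 is an unadjusted intention-to-treat GEE regression with robust variance. Model 2 adds the design effect. Model 3 further adjusts for measured differences between the study groups that were not foreseen.

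On what enters Model 3, the section says "Model 3 will include all covariates that are statistically significant and judged as important differences between the study group". It adds a caution against counting a difference that is significant only because the sample is large. The same sentence then says these covariates are identified by a backward stepwise Wald analysis, which "removes the covariate least associated with the outcome, and continues in that manner to remove covariates not significantly associated with the outcome" at α = 0.05.

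The section does not list the candidates. It compares socio-demographic, reproductive health and facility characteristics by arm, using chi-square and Student's t-tests. The facility data already held are described under Study design, where the matching list of six factors ends with "baseline PTB rate, and 6) availability of key screening tests".

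**The concern.** Imbalance between arms and association with the outcome are separate properties of a covariate. A Wald test of a covariate's coefficient in the outcome model does not measure whether the arms differ on it. If the elimination step decides, a covariate that differs between arms can be dropped. If the imbalance clause decides, the stepwise procedure is not what identifies the covariates. The text supports both readings, and they lead to different models.

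The outcome data also choose the adjustment set. For facility-level covariates, those data amount to 36 facility means. Backward elimination tends to keep covariates that happen to fit chance variation in those means, which makes the residual variance look too small when group care is then tested. Because the procedure is repeated for each outcome, the adjusted estimates may not be adjusted for the same things. The clause on judged importance has no criterion attached.

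At stake are the p-values and confidence intervals of the fully adjusted results, and their comparability across outcomes.

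**Working it through.** **Inputs, from Sample size and Study design.** There are 36 facilities, 18 per side. Significance is 5% (two-sided assumed; the article does not say) and power is 80% for a 0.5-week difference. The "standard deviation of GA at delivery is no larger than 4.3 weeks under both intervention and control arms", and the ICC "will be no larger than 0.01".

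**The plan's own figure.** The unclustered size per side is n0 = 2 × (1.960 + 0.842)² × 4.3² / 0.5² = 1,161. Per facility, m = n0(1 − ICC) / (k − n0 × ICC).
- k = 18: 1,161 × 0.99 / (18 − 11.61) = 180.
- k = 17 (one facility per side deducted): 1,161 × 0.99 / (17 − 11.61) = 213.2, so 214, as stated.
- 214 / 0.70 = 305.7, so 306, as stated; 306 × 36 = 11,016.

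With m = 214, power is 80.0% on a t reference with 34 df and 82.2% on a normal reference. The stated 214 is therefore consistent with a small-sample allowance in the sample size, although the article does not say how it was obtained.

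**Simulation setting.** No effect of group care, 36 facilities of 214 women, variance of a facility mean = 4.3² × (0.01 + 0.99/214) = 0.270, backward removal at 0.05, group care always kept. The number of candidates is an assumption. Study design and Study setting name enough facility descriptors for about 12 df: six matching factors, distance to hospital, urban or rural, and five districts (6 + 1 + 1 + 4).

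**Selection alone.** Facility means, exact t test, pairing not modelled, 8,000 runs per row (Monte Carlo SE about √(0.05 × 0.95 / 8,000) = 0.24 points):

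| Facility-level candidates | All kept, fixed | Backward selected |
|---|---|---|
| 3 | 4.8% | 5.5% |
| 6 | 4.9% | 6.2% |
| 8 | 5.4% | 7.0% |
| 10 | 4.9% | 7.2% |
| 12 | 4.9% | 7.6% |
| 15 | 4.9% | 9.0% |
| 20 | 5.4% | 12.4% |

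Two further simulations with pair-randomised facilities gave 5.5%, 6.0-6.3% and 7.2-8.0% for 4, 8 and 12 candidates.

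**Adding an uncorrected robust variance.** Pair-randomised facility means, normal reference:

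| Facility-level candidates | Backward selected | Same covariates, fixed |
|---|---|---|
| 4 | 6.9-7.4% | 8.1-8.4% |
| 8 | 9.0% | 11.1-11.4% |
| 12 | 10.9-11.8% | 14.9-15.3% |

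A woman-level simulation with a cluster-robust sandwich (1,500 runs) shows the same ordering. Selected against fixed was 9.4% and 10.9% with 6 candidates, 11.6% and 14.1% with 10, and 14.8% and 18.8% with 15. With a small-sample correction, 10 candidates gave 7.2% selected and 5.9% fixed. The higher rates thus come mainly from the variance estimator.

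**Woman-level candidates only, uncorrected sandwich.** Ten noise covariates gave 5.3% (unadjusted 5.2%) and twenty gave 7.1% (unadjusted 6.8%). Twenty predictive covariates gave 8.2%, and the same model without selection also gave 8.2%. Selection adds about nothing.

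**Imbalance screen first.** A facility-level screen at p < 0.05 left 6.2-6.9%, against 6.0-6.8% unadjusted. If the screen is instead an ordinary woman-level test on 36 × 214 = 7,704 women, ignoring clustering, about 85% of pure-noise facility covariates pass. With the uncorrected variance, Model 3 then gave 8.2% with 8 candidates and 10.1% with 12.

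**Short fixed list.** Two facility covariates fixed in advance, tested on t with 36 − 4 = 32 df, gave 4.4-5.7%.

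**The case against.** The strongest reply is that the sentence does require an important difference between study groups, so it can be read as an imbalance screen followed by elimination. On that reading a balanced covariate would not be kept, and with a facility-level screen the error rate barely moves. This stands in part. A reader might infer that imbalance plays no role in Model 3, and the text does not support that. What remains is that the procedure said to identify the covariates works on a different criterion, and that the screen is settled only by judgement.

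A reader might also infer that stepwise selection doubles the false-positive rate. The documents do not support that. No candidate count is given. Facility-level adjustment is mentioned separately, as multi-level analyses to be considered, and the caution about large samples suggests woman-level covariates. Selection alone doubles the rate only somewhere between 15 and 20 facility-level candidates, more than the roughly 12 df the article names. The rates of 10% or more at 8-12 candidates depend on an uncorrected robust variance. That is an assumption too, since the article says only that robust variance is used and a correction may be specified in an analysis plan that is not shown.

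Nor does the article make Model 3 the decisive test. The unadjusted Model 1 comes first for the primary outcome, and a comparison with TMLE is proposed. It also does not say whether inference will allow for selection, or whether those judging importance will know the allocation or the outcomes. Neither should be presumed.

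**Conclusion.** The point holds as a mismatch between purpose and procedure. Model 3 is meant to correct for differences between arms, but its stated algorithm selects on the outcome, with no criterion for the judgement step and possibly a different covariate set for each outcome.

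From a nominal 5%, the cost of selection itself is roughly 0.5 to 3 points with 4-12 facility-level candidates, and about nil with woman-level candidates only or with a facility-level imbalance screen first. These sizes rest on the plan's upper-bound SD and ICC, a two-sided 5% test and an assumed number of candidates. The primary conclusion would be affected only if Model 3 were preferred to Model 1.

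Fixing the covariates is not enough by itself. Under an uncorrected robust variance, a long fixed list is no better than a selected one, so the list must be short and paired with a small-sample reference.

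**What to change.** Delete the backward stepwise step and the clause on judged importance. Define Model 3 by one short list of baseline covariates, used for every outcome and retained whatever their p-values. It could, for example, be drawn from the matching factors already collected plus a few baseline maternal characteristics. Test the group-care term with a t reference on facility-based degrees of freedom or a bias-corrected robust variance. Keep the proposed TMLE as the place for data-adaptive adjustment, labelled as a sensitivity analysis.

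Study status reports that data collection has ended and analysis is under way. The list should therefore be dated, with a statement of whether it was set before outcomes were seen by arm.

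The cost is a change of wording, with no new data. The downside is that a covariate later found to be imbalanced enters only as a sensitivity analysis.

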### Trial monitoring

The trial will be monitored by a five-member independent Data and Safety Monitoring Board (DSMB). DSMB members include two obstetrician-gynecologists, one pediatrician, one midwife, and one biostatistician; two of these members are Rwandan and all are East African. The DSMB charter is available as
*Extended data*: File 14
^18^.

The DSMB will convene after trial initiation, with subsequent meetings at least every six months and will perform up to two interim data analyses. The DSMB has agreed on the Haybittle–Peto rule
^28,
29^ as the stopping boundary to be used for interim analyses. In the case that application of the Haybittle-Peto rule results in a recommendation to terminate the trial, the DSMB will consult with the study investigators and other partners to make a final decision. Adverse events will be reported immediately to the ethical review boards and will be summarized and presented to the DSMB at each of their meetings.

### Ethics approval

This study protocol was reviewed and approved by the Rwanda National Ethics Committee (No 0034/RNEC/2017) and the UCSF Institutional Review Board (No 16-21177). A waiver of parental consent for any adolescent 15 years of age or older was granted by the Rwanda National Ethics Committee, allowing adolescents over 15 to consent to participation in primary and secondary interventions and data collection and analysis.

All members of the research team were trained in ethical practices in human research. Research staff will emphasize that participation in the study is voluntary and that refusal to participate in the study will not results in negative repercussions. If any modifications to the study protocol are made, these modifications will be submitted to both ethical review boards for approval. This study was registered on ClinicalTrials.gov, ID
NCT03154177 on May 16, 2017.

### Consent to participate

Prior to enrollment or interview, data collectors will administer consent to participants. Each participant will be given the opportunity to read a written consent form or if illiterate have it read to her/him by a witness
*(see Extended data*: Files 12 and 13f)
^18^. The consent statement will explain the study objectives, requirements, potential risks, privacy and ethical obligations of the research team. The participant will complete the consent process by agreeing or disagreeing to the consent statement. The consent form will be administered in Kinyarwanda (the local language) and only participants who agree to participate and sign the written consent form will participate.

### Dissemination of data and materials

Final datasets will be jointly owned by all investigators. As per our funder’s open access policy, de-identified datasets and statistical code will be made publicly available on request once we have published on our primary outcomes.

Results will be disseminated in a national dissemination meeting, at international conferences and through publication. No specific efforts will be made to reach participants.

### Study status

Enrollment and data collection started on May 25, 2017 and ended on December 31, 2018. Data processing and analysis are currently being conducted.

## Discussion

In WHO’s 2016
*Recommendations on antenatal care for a positive pregnancy experience*, the authors write that

“communication and support functions of ANC are key, not only to saving lives, but to improving lives, health-care utilization and quality of care. Women’s positive experiences during ANC and childbirth can create the foundations for healthy motherhood.”
^16^

Group ANC seems to hold the promise of improved effectiveness of health message communication in a peer-to-peer education model, enhanced support and cohesion among pregnant women in a community, and increased satisfaction with and uptake of ANC.

This trial will provide much-needed evidence to advance the field. First, it will examine the health effects of group ANC in the context of low- and middle-income countries (LMICs) and within an intent-to-treat approach almost identical to routine health service delivery in that context. Second, it is the first to test group care as applied to the four-visit Focused ANC model widely used in LMICs, and thus will provide evidence about whether this innovative model can improve adherence to the four-visit schedule. Third, the trial will also report whether the group care model impacts attendance at six-week PNC in a context in which PNC attendance is currently very low. Fourth, the trial will also provide feasibility evidence regarding the use of CHWs as co-facilitators in group care. Lastly, this trial further provides additional insight into the relative effects of basic obstetric ultrasound at health centers and urine pregnancy testing at the community level on early uptake of ANC and adherence to the recommended visit schedule.

This is the largest trial of group ANC to date, powered to detect a difference in GA at birth. The implementation of group ANC at this scale within the practical realities of a national maternity care system will inform global stakeholders as they make decisions at the policy, system, facility, and individual levels about the optimal ANC service model for the mothers and newborns they serve.

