## Methods

### Study aims

The primary aim of this study is to evaluate the effect of group antenatal care on gestational age at birth, at a cluster level. The secondary aims of this study are to determine the effects of: group antenatal care, screening obstetric ultrasound, and urine pregnancy testing in the community on antenatal care attendance and women’s and providers’ experience of antenatal and postnatal care; group antenatal care on preterm birth rates; group antenatal care on mode of birth; and group antenatal care on the outcomes of neonates at 42 days after birth, specifically among preterm neonates.

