Figure 1. Arm 1 delivers standard ANC/PNC care only and is the pure control. Arm 2 delivers standard ANC and PNC care, with the addition of early pregnancy testing in the community and obstetric ultrasound performed by primary ANC providers. Arm 3 delivers group ANC/PNC, and Arm 4 delivers group ANC/PNC with the addition of early pregnancy testing and ultrasound. In health centers randomized to group care (Arms 3 and 4), this model will follow the opt-out standard of care for facility-based ANC and PNC. This design makes it possible to analyze differences between group care and standard care and also to assess if those effects are mediated by early pregnancy testing in the community or the availability of ultrasound (especially for early GA assessment) at the health center.

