Those providers and CHWs associated with sites randomized to group ANC were invited to a three-day training workshop on a rotating basis to minimize the impact on service provision. This workshop brought providers and CHWs together in joint training activities for the first time ever. Training occurred in large- and small-group circles to replicate as closely as possible the principles of successful group care. Activities focused on principles of adult learning, facilitation skills, a review of the Rwanda ANC/PNC packages of care, health assessment skills, how to organize and facilitate a group visit, and role-play practice of each of the group ANC/PNC curriculum discussion topics with feedback and re-practice.

These new group ANC facilitators were trained in all aspects of model fidelity by a team of six Rwandan group ANC Master Trainers
^22^. The Master Trainers, five midwives and one physician, who all have separate employment, were recruited based on their excellent facilitation skills, expertise in maternal and newborn health, and commitment to the project. The Master Trainers will make scheduled visits to each health center providing group ANC, with decreasing frequency over time, and unscheduled visits will be made as needed. During these visits, Master Trainers will observe group ANC as it is delivered and collect data about model fidelity. They will also offer supportive feedback and will model for group ANC facilitators how to plan for and debrief after each visit.

Study sites assigned to either Arm 2 or Arm 4 are randomized to introduce basic obstetric ultrasound by ANC providers at the health center and urine pregnancy testing by CHWs in the community (
Figure 1). The objective of screening ultrasound at the health center level is to more accurately assign the EDD, but providers are also trained to screen for gross abnormalities. The goal of community-based pregnancy testing is to engage women in earlier ANC attendance, which in turn may identify and promote early referral of at-risk pregnancies for physician consultation at district hospitals.

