### Outcomes and processes for comparison

This trial will evaluate both outcomes and processes. The primary study outcome is GA at birth. GA at birth will be calculated using the EDD assigned by ANC providers using the best obstetric estimate. In health centers randomized to implement basic obstetric ultrasound, this tool will be used to optimize GA assignment. In addition, postnatal measurements of every newborn will be used to estimate GA at birth and assign a corrected GA if needed.

Secondary outcomes include attendance, PTB rate, and neonatal mortality and morbidity among preterm neonates. Outcomes, including analysis metrics, method of aggregation and time points are summarized in
Table 2.

**Table 2. T2:** Outcomes.

Measurements variable	Analysis metric	Aggregation	Time Point
Primary Outcomes			
GA at birth	Average weeks completed	Health center	At delivery
Secondary Outcomes			
Preterm birth	Yes/no <37 weeks GA	Rate compared across arms	At delivery
Mortality among preterm neonates	Alive/dead	Rate compared across arms	At 28 days and 42 days, measured at six week follow up visit
Attendance at four ANC visits	Yes/no	Proportion compared across arms	At Delivery
Attendance at ANC one <14 weeks GA	Yes/no	Proportion compared across arms	At ANC 1
Attendance at PNC at six weeks	Yes/No	Proportion compared across arms	Record review at 12 weeks post EDD
Women identified as being high risk at ANC	Yes/no	Proportion compared across arms	From 1 ^st^ ANC until day of delivery
Caesarean section	Yes/no	Proportion compared across arms	At delivery
Newborn morbidities: jaundice, rapid breathing, fever, pneumonia, hypothermia, cord infection	Any reported: Yes/no	Proportion compared across arms	Reported in Rapid SMS (community reporting system) or neonatal register by 28 days of age
Other Outcomes			
Acceptability	Qualitative data on acceptability to women and providers	Qualitative reporting	At nine and 18 months
Satisfaction with care, locus of control, perceived social support, perceived stress, and depressive symptoms	Survey data	Comparison across arms	Baseline (at enrollment) and eight weeks after birth
Postnatal health behaviors, including family planning uptake, insecticide- treated mosquito net use, and breastfeeding	Survey data	Comparison across arms	Eight weeks after birth

GA, gestational age; ANC, antenatal care; PNC, postnatal care; EDD, estimated date of delivery.

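### Ultrasound and community pregnancy testing are allocated only as one package, so their separate or relative effects cannot be estimated, and contrasts across ultrasound status mix effect with dating method for outcomes defined by gestational age

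*Protocol article*

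**What the plan says.** Allocation (Protocol article, Study design): one pair in each quadruple was assigned to "additionally implement basic obstetric ultrasound at the health center and early pregnancy testing at the community level and the other was not". Study interventions confirms the arms: "Study sites assigned to either Arm 2 or Arm 4 are randomized to introduce basic obstetric ultrasound by ANC providers", with urine pregnancy testing by community health workers in the same sites. No arm receives one component without the other.

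Claims about the components:
- Study aims: to "determine the effects of: group antenatal care, screening obstetric ultrasound, and urine pregnancy testing in the community on antenatal care attendance" and on women's and providers' experience.
- Study design: the four-arm layout is said to make it possible to "assess if those effects are mediated by early pregnancy testing in the community or the availability of ultrasound".
- Discussion: the trial is said to inform on the "relative effects of basic obstetric ultrasound at health centers and urine pregnancy testing at the community level".

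Dating (Outcomes and processes for comparison): "In health centers randomized to implement basic obstetric ultrasound, this tool will be used to optimize GA assignment". The same paragraph adds that newborn measurements, taken for every newborn, will be used to estimate GA at birth and to correct it where needed.

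Analysis (Statistical analyses): the main comparison pools Arms 1+2 against Arms 3+4, and "Subanalyses by study arm will be conducted".

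**The concern.** Two factors that are always switched on together leave no data from which to divide their joint effect. Three sections nonetheless word the aims or expected insights as if this were possible. A policy reader could then credit ultrasound alone, or pregnancy testing alone, with a change in attendance that the trial can credit only to the pair. The cost and logistics of the two are quite different, so the attribution matters.

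The word mediated adds a second difficulty. A mediator is something that group care changes and through which it acts. Availability of the package was set by its own randomisation, whatever the group-care assignment. The pregnancy test also comes before the first ANC visit, at the end of which group care is offered. The design supports a different question: whether the group-care effect is larger or smaller where the package is present.

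The third difficulty is measurement. The package includes the tool that dates the pregnancy. An outcome defined by a GA cut-off can therefore differ between package and non-package arms with no change in behaviour or biology. Early ANC attendance is such an outcome, and it falls under a stated aim for the package.

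**Working it through.** **1. Can the components be separated?** Write the mean in each arm as μ + γG + αU + βP, with G group care, U ultrasound and P pregnancy testing.

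| Arm | G | U | P | Mean |
|---|---|---|---|---|
| 1 | 0 | 0 | 0 | μ |
| 2 | 0 | 1 | 1 | μ + α + β |
| 3 | 1 | 0 | 0 | μ + γ |
| 4 | 1 | 1 | 1 | μ + γ + α + β |

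The U and P columns are identical, so the four-column design matrix has rank 3. Replacing (α, β) by (α + c, β − c) leaves every mean unchanged for any c. Only α + β is estimable. Timing does not separate them: the Introduction says ultrasound is itself meant to bring women to ANC earlier and more often, so earlier attendance cannot be assigned to testing alone.

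**2. Which contrasts carry a dating shift?** Suppose ultrasound dating moves recorded GA by b weeks on average in Arms 2 and 4.

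| Contrast | Bias |
|---|---|
| 2−1, 4−3, 4−1 | b |
| 3−2 | −b |
| 3−1, 4−2 | 0 |
| (3+4)/2 − (1+2)/2 | b/2 − b/2 = 0 |
| Interaction (4−2) − (3−1) | 0 |

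Four of the six arm pairs are affected. The primary contrast is not.

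**3. Size for first ANC visit before 14 weeks (Table 2).** The Introduction gives 56% entering before 16 weeks. Normality and an SD of 4 weeks are assumptions.
- Mean = 16 − 4 × 0.151 = 15.40 weeks.
- Share before 14 weeks = Φ((14 − 15.40)/4) = 36.4%.
- Recorded GA shifted by ±0.25 week: 34.0% or 38.7%, about 2 points.
- Shifted by ±1 week: 27.5% or 46.1%, about 9 to 10 points.

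Table 3 uses a 16-week cut-off for the corresponding indicator. There a 1-week shift moves 56% to about 46% or 66%, again about 10 points.

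**4. Size for GA at birth across ultrasound status.** Inputs from Sample size: SD 4.3, ICC 0.01, 214 observations per facility, 36 facilities. The plan's own figure reproduces. The design effect is 1 + 213 × 0.01 = 3.13. With 18 facilities per side, SE = 4.3 × √(2 × 3.13/(18 × 214)) = 0.173, and a two-sided 5% t test on 34 df has 80.0% power for 0.5 week at 214 per facility.

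For two single arms (36/4 = 9 facilities each), SE = 4.3 × √(2 × 3.13/(9 × 214)) = 0.245. With no true effect, the chance of a significant result is Φ(b/SE − 1.96) + Φ(−b/SE − 1.96):

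| Assumed shift b (weeks) | Chance of significance |
|---|---|
| 0 | 5% |
| 0.1 | 7% |
| 0.25 | 18% |
| 0.5 | 53% |
| 1.0 | 98% |

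These use the normal approximation and take no credit for the newborn-based correction.

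**5. Precision of what remains estimable.** For the interaction on GA, SE = 4.3 × √(4 × 3.13/(9 × 214)) = 0.347. Power for 0.5 week is about 30%, and the difference detectable with 80% power is about 0.97 week.

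**The case against.** The best defence is that the aims are modest. Study aims limits the ultrasound and testing questions to attendance and experience. GA, preterm birth and mode of birth are aims for group care only, and the Discussion sentence also concerns uptake and adherence. This stands: no stated aim asks for a package effect on GA at birth. The dating point for GA and preterm birth therefore rests on the unspecified by-arm subanalyses. It bears directly on a stated package aim only for ANC timing.

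It can also be said that newborn measurements, taken in every arm, bring the dating methods closer together. That may reduce the shift for GA at birth, although when a correction is needed is not defined in the article. It cannot help with GA at the first ANC visit.

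A reader might go further in three ways that the documents do not support.
- *All by-arm GA comparisons are unidentifiable, or the primary result is compromised.* Arms 1 and 3 share a dating method, as do Arms 2 and 4, and the balanced layout cancels an additive shift in the primary contrast and the interaction.
- *Tests of the package would have inflated type I error because it was allocated to pairs.* No section says facilities will be treated as independent for that contrast. With correlation rp within pairs and rq between pairs of a quadruple, the variance relative to independence is 1 + rp − 2rq. This exceeds 1 only if rq is below rp/2, which the documents do not tell us.
- *Not naming the contrast of Arms 2+4 against 1+3 is a defect.* That is detail an analysis plan commonly supplies.

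**Conclusion.** The separate and relative effects of ultrasound and pregnancy testing, as worded in Study aims and the Discussion, cannot be estimated. This follows from the allocation alone, needs no assumption, and no sample size or modelling cures it. The mediation wording in Study design describes a question the layout does not address; effect modification by the package is the one it does.

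The dating problem is real but confined to contrasts across ultrasound status: first ANC visit before 14 weeks, and by-arm GA or preterm birth for Arms 1 and 2, 1 and 4, 2 and 3, and 3 and 4. Its size is unknown. The 2 to 10 point range for early ANC depends on the assumed normal distribution, the SD of 4 weeks, the 56% survey figure, and a shift of 0.25 to 1 week. The cancellation in the primary contrast and the interaction assumes that the shift is additive and equal in Arms 2 and 4. The stated sample size is unaffected.

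**What to change.** - **Study aims and Discussion:** claim only the effect of the combined ultrasound plus pregnancy-testing package, and remove the reference to relative effects.
- **Study design (and the Figure 1 legend, which repeats the wording):** replace mediation by one component or the other with effect modification (interaction) by the package.
- **GA-defined outcomes compared across ultrasound status:** report results under a dating method common to all four arms, such as GA from last menstrual period where recorded, alongside the best-estimate GA. Attribute a difference to the package only if both agree.
- **By-arm GA and preterm birth:** say that Arm 3 against 1 and Arm 4 against 2 are the pairs with a shared dating method.

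Cost: Study status reports that enrollment and data collection have ended and analysis is under way, so this is a change of wording plus a parallel derivation, with no new recruitment. The claims become narrower, and the interaction on GA will be imprecise. Dating by last menstrual period is noisier, and earlier pregnancy testing might itself change recall of it, so it serves as a check and is not error-free. Table 3 lists that GA only for GA at birth, so its availability at the first ANC visit must be confirmed.
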